**Methods and analysis:**

This study is a single-blind, randomized controlled trial. Fifty-six adults with MDD will be recruited and randomly assigned (1:1) to receive either active sequential bilateral Dorsolateral Prefrontal Cortex (DLPFC) aTBS (10 weekday sessions; 3600 pulses per session) consisting of continuous theta-burst stimulation (cTBS) applied to the right DLPFC followed by intermittent theta-burst stimulation (iTBS) applied to the left DLPFC, or sham stimulation. The primary outcomes will be response and remission rates based on the 17-item Hamilton Depression Rating Scale (HAMD-17). Secondary outcomes will include the Beck Depression Inventory-II (BDI-II), the Columbia Suicide Severity Rating Scale (C-SSRS), and electroencephalography (EEG)-derived electrophysiological markers of cognitive processing (P300). Safety and tolerability will be systematically evaluated throughout the study using the Treatment Emergent Symptom Scale (TESS) to record stimulation-related adverse events. Outcome measures will be assessed at baseline, immediately after the 10-day intervention, and at 2-week and 4-week follow-ups to evaluate the short-term sustainability of treatment effects.

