Growing evidence suggests that suicidal ideation in MDD patients is associated with impairments in cognitive control, attentional regulation, and emotional processing, primarily involving the prefrontal-limbic circuitry (18, 19). Investigating these neurophysiological mechanisms may provide objective biomarkers for identifying suicide risk and evaluating treatment efficacy. Electroencephalography (EEG), with its high temporal resolution, enables direct assessment of cortical excitability and cognitive dynamics under neuromodulation. Among EEG-derived event-related potentials, the P300 component—typically elicited by an auditory oddball paradigm—serves as a reliable indicator of attentional resource allocation and information processing (20, 21). Consistent evidence shows reduced P300 amplitude and prolonged latency in depressed patients, reflecting diminished cognitive efficiency and prefrontal dysfunction (22). Moreover, effective antidepressant interventions—including high-frequency repetitive transcranial magnetic stimulation (rTMS)—have been shown to normalize P300 parameters in parallel with clinical improvement (23). These findings support the use of P300 as a sensitive electrophysiological marker of treatment response. Therefore, evaluating P300 changes before and after sequential aTBS may provide crucial insights into the neurophysiological mechanisms underlying its therapeutic effects, thereby helping to elucidate the intervention’s neurophysiological principles of action.

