### Objectives

The primary objective of this randomized controlled trial is to evaluate the clinical efficacy of sequential accelerated Theta Burst Stimulation (aTBS) in adults with MDD. Our central hypothesis is that, compared to sham stimulation, sequential aTBS will induce a faster and more significant alleviation of depressive symptoms, with this therapeutic effect remaining significant throughout the subsequent 2-week and 4-week follow-up periods. A secondary objective of this study is to systematically evaluate the safety, tolerability, and adverse event profile of sequential aTBS in the target population. For this safety assessment, the Treatment Emergent Symptom Scale (TESS) will be administered to capture and characterize common adverse events, including headache, dizziness, nausea, scalp discomfort, and muscle twitching. For mechanistic exploration, this study will employ high-temporal-resolution EEG to capture the P300 event-related potential as a neurophysiological indicator, aiming to elucidate the mechanisms by which aTBS modulates cortical excitability and cognitive-emotional processing, thereby identifying potential biomarkers for future treatment strategies.

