## Materials and methods

### Study design

This randomized, sham-controlled clinical trial was approved by the Ethics Committee of Wuxi Mental Health Center and prospectively registered in the Chinese Clinical Trial Registry (ChiCTR; official website: www.chictr.org.cn, Registration No.: ChiCTR2500109181). All procedures will adhere to the principles of the Declaration of Helsinki and the Guidelines for Good Clinical Practice (GCP). Reporting will follow the SPIRIT 2025 recommendations, and the completed SPIRIT checklist is available in **Supplementary Material S1**.

This trial will be conducted at Wuxi Mental Health Center between September 2025 and August 2027. The assessment and screening will be conducted by two practicing physicians from Wuxi Mental Health Center. Eligible participants will be randomly allocated (1:1) to receive either active sequential accelerated theta burst stimulation (aTBS; 3,600 pulses per session, 10 sessions total) or sham stimulation. Outcome measures will include the 17-item Hamilton Depression Rating Scale (HAMD-17) (24), Beck Depression Inventory (BDI-II) (25), Columbia Suicide Severity Rating Scale (C-SSRS) (26), Treatment Emergent Symptom Scale (TESS) (27) and event-related potential P300. All assessments will be administered at baseline (T0), immediately after the final stimulation session (T1), and at 2-week (T2) and 4-week (T3) follow-ups. A detailed flow diagram of the trial is shown in **Figure 1**, and the trial schedule is presented in **Table 1**.

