**Figure 1 f1:**
[figure not shown]
CONSORT flow diagram of the study protocol; Patient screening; Depressed patients (n=56); Randomized allocation; Active stimulation group (n=28); Sham stimulation group (n=28); T0, baseline (randomization); T1, post-intervention; T2, 2-week follow-up; T3, 4-week follow-up; HAMD-17, 17-item Hamilton Depression Rating Scale; BDI-II, Beck Depression Inventory-II; C-SSRS, Columbia-Suicide Severity Rating Scale; aTBS, accelerated theta-burst stimulation.

**Table 1 T1:** Detailed trial schedule.

	Study period							
	Enrollment	Allocation	Post-allocation				Follow-up 1	Follow-up2
Time point	Day-1	Day 0	AFT	Day1	~	Day 10 (Intervention period)	Week2	Week4
Enrollment:								
Eligibility screen	×							
Informed consent	×							
Randomization	×							
Allocation		×						
Interventions:								
Conventional treatment + sequential aTBS								
Conventional treatment + sham sequential aTBS								
Assessments:								
HAMD-17		×				×	×	×
BDI-II		×				×	×	×
C-SSRS		×				×	×	×
P300		×				×		
Case report forms	×							
Adverse events								
TESS								
Blinding			×					
TASS	×							
ATHF	×							

AFT; Immediately post-allocation (after randomization and before the first intervention); HAMD-17, 17-item Hamilton Depression Rating Scale; BDI-II, Beck Depression Inventory-II; C-SSRS, Columbia-Suicide Severity Rating Scale; P300, Electroencephalography; ATHF, Antidepressant Treatment History Form; TASS, Transcranial Magnetic Stimulation Safety Screen; TESS, Treatment Emergent Symptom Scale ×, occurs at that time.

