#### Analysis of clinical data

All statistical analyses will be conducted using SPSS version 26.0. Continuous variables will be presented as means ± standard deviations or medians (interquartile ranges), depending on distribution, and compared using independent samples t-tests or Mann-Whitney U tests, as appropriate. Categorical variables will be expressed as frequencies (%) and analyzed using Chi-square or Fisher’s exact tests. A repeated-measures analysis of variance (ANOVA) will be applied to evaluate longitudinal changes in each outcome, with group (active vs sham) as the between-subject factor and time (baseline, post-intervention, follow-up) as the within-subject factor. If the assumption of sphericity is violated according to Mauchly’s test, the Greenhouse-Geisser correction will be applied. Significant interactions will be followed by Bonferroni-adjusted simple-effects comparisons to determine between-group differences at each time point and within-group changes across time.

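### P300 is scheduled at four visits in the text but at two in Table 1, and the three time levels named for the ANOVA match no outcome's visits

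*Protocol article*

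**What the plan says.** **Visits in the text.** The outcome list under Study design ends with "Treatment Emergent Symptom Scale (TESS) (27) and event-related potential P300", and a following sentence gives one schedule for everything: "All assessments will be administered at baseline (T0), immediately after the final stimulation session (T1), and at 2-week (T2) and 4-week (T3) follow-ups". The abstract's Methods and analysis paragraph names P300 as a secondary outcome and then states: "Outcome measures will be assessed at baseline, immediately after the 10-day intervention, and at 2-week and 4-week follow-ups". Neither place makes an exception for EEG.

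**Visits in Table 1** ("Detailed trial schedule"). HAMD-17, BDI-II and C-SSRS each have crosses at Day 0, Day 10, Week 2 and Week 4. P300 has crosses at Day 0 and Day 10 only. The last two columns are headed as two separate follow-ups.

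**Purpose of P300.** The Introduction says that "evaluating P300 changes before and after sequential aTBS may provide crucial insights", which fits a two-visit schedule.

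**Analysis.** Under Analysis of clinical data: "A repeated-measures analysis of variance (ANOVA) will be applied to evaluate longitudinal changes in each outcome", with "time (baseline, post-intervention, follow-up) as the within-subject factor". Significant interactions are followed by Bonferroni-adjusted comparisons of the groups at every time point. The Analysis of EEG section defines P300 amplitude and latency but leaves the statistical model open.

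**Hypothesis.** The Objectives section expects a faster and larger improvement in depressive symptoms, "with this therapeutic effect remaining significant throughout the subsequent 2-week and 4-week follow-up periods".

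**The concern.** There are two mismatches, and they have different consequences.

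The first concerns data collection. The text and the schedule table disagree on whether EEG is recorded at weeks 2 and 4. Staff usually work from the schedule table, and an EEG that was not recorded at a follow-up visit cannot be recovered later. The final report would then lack data that the abstract and Study design section announce.

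The second concerns the time factor of the repeated-measures ANOVA. Three levels are named, but no outcome is measured at three visits under either schedule. It is therefore not fixed whether T2 and T3 enter as separate levels. That matters because the stated hypothesis covers both follow-ups, and because the choice changes the degrees of freedom and the number of Bonferroni comparisons. It should not be left until the data have been seen.

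If P300 does have only two visits, there is also a simple gain to be had: the baseline recording is already planned and can be used as a covariate.

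**Working it through.** **1. Visits per outcome, side by side**

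| Outcome | Abstract and Study design | Table 1 | Levels named for the ANOVA |
|---|---|---|---|
| HAMD-17, BDI-II, C-SSRS | 4 | 4 | 3 |
| P300 | 4 | 2 | 3, if that section covers P300 |

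For the scales, text and table agree on four visits. For P300 they do not. Loss of table marks in the PDF reading is an unlikely explanation: the P300 row keeps two crosses, the neighbouring rows keep all four, and the Introduction's pre/post description fits two visits.

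**2. What the number of time levels changes**

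With N = 56 completers, two groups and m levels, the group-by-time interaction has (m − 1) and (N − 2)(m − 1) degrees of freedom:

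- m = 2: 1 and 54
- m = 3: 2 and 108
- m = 4: 3 and 162

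Within one group, the pairwise time comparisons number m(m − 1)/2: 3 for three levels and 6 for four. If Bonferroni is applied over that set, the threshold is 0.05/3 = 0.0167 or 0.05/6 = 0.0083.

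**3. Does the sample size show which m was meant?**

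No. The Sample size section gives an F-test, d = 0.38, 80% power and 50 participants, but neither the number of measurements nor the within-subject correlation. Taking f = d/2 = 0.19, the within-between interaction and an assumed ρ = 0.5, the required N is 58, 48 and 40 for m = 2, 3 and 4. A total of 48 to 52 is also reached with m = 2 at ρ of about 0.55, and with m = 4 at ρ of about 0.35 to 0.40. The figure of 50 is therefore compatible with any of the three.

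**4. P300 with two visits**

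A two-level group-by-time ANOVA can be fitted. Its interaction test is identical to a t-test on the change score; in simulated data with 28 per group, F = t² = 5.405.

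Let the variance be σ² at both visits (assumed) and the T0–T1 correlation be ρ (assumed; the protocol gives none):

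- Change score: 2σ²(1 − ρ)
- T1 adjusted for T0 by ANCOVA: σ²(1 − ρ²)
- Ratio: (1 − ρ²) / [2(1 − ρ)] = (1 + ρ)/2

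At ρ = 0.5 the ratio is 0.75, so the variance is 25% lower. At ρ = 0.7 it is 0.85, 15% lower. This ignores the single degree of freedom spent on the slope. For the 50 participants planned after dropout, the gain is equivalent to 50/0.75 ≈ 67 or 50/0.85 ≈ 59 analysed by change score.

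**The case against.** Three objections carry weight.

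**The time levels may be shorthand.** The three labels can be read as study phases. The same section promises group comparisons at every time point, Study design and the Figure 1 legend define T2 and T3 as distinct, and Table 1 has two follow-up columns. A reader might infer that the follow-ups have to be pooled or one of them dropped. The protocol says neither. What stands is that the named levels fit no outcome and the intended ones are not stated.

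**The ANOVA may not be meant for P300.** It appears under the heading for clinical data, and the EEG section leaves its own model open. Leaving that model to an analysis plan that is not shown is not a fault. A reader might also infer that the stated model cannot be fitted to P300. That is so only for a literal three-level factor under Table 1; with two levels the ANOVA fits without difficulty.

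**ANCOVA is an efficiency choice.** The two-level ANOVA is a valid analysis in a randomized comparison, and the Discussion calls the EEG analysis exploratory. This stands: the ANCOVA suggestion improves precision and corrects no error.

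None of these objections touches the disagreement over which visits include P300.

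**Conclusion.** The P300 contradiction is certain: four visits in the abstract and Study design, two in Table 1. It decides whether week-2 and week-4 EEG recordings exist.

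The time-factor point holds in a limited form. Three named levels match no outcome's schedule, and read literally they would not test the hypothesis separately at 2 and 4 weeks. The documents do not show that this literal reading is intended, so the point is an ambiguity to be closed and not a demonstrated error in the analysis.

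The possible gain from ANCOVA on a two-visit P300 is a variance of 0.75 to 0.85 of that of the change-score comparison for ρ between 0.5 and 0.7. It rests on assumed correlations and equal variances at T0 and T1.

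The primary comparison of response rates after the intervention is not affected. The matter should be corrected, but it does not threaten the trial's main result.

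**What to change.** 1. **P300 visits.** Make the abstract, Study design and Table 1 agree. Limiting the text to T0 and T1 for P300 costs only wording and fits the Introduction. Adding T2 and T3 to Table 1 would cost up to 2 × 56 = 112 further EEG recordings, as many again as Table 1 now plans.
2. **Time levels.** In Analysis of clinical data, name four levels (T0, T1, T2, T3) for HAMD-17, BDI-II and C-SSRS, and state that the group difference is reported separately at T2 and at T3. This costs wording only.
3. **P300 model.** If P300 is recorded at T0 and T1 only, analyse T1 amplitude and T1 latency by ANCOVA with group as factor and the T0 value as covariate. This is one change to the analysis and needs no recording beyond the two already in Table 1.

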**Figure 1 f1:**
[figure not shown]
CONSORT flow diagram of the study protocol; Patient screening; Depressed patients (n=56); Randomized allocation; Active stimulation group (n=28); Sham stimulation group (n=28); T0, baseline (randomization); T1, post-intervention; T2, 2-week follow-up; T3, 4-week follow-up; HAMD-17, 17-item Hamilton Depression Rating Scale; BDI-II, Beck Depression Inventory-II; C-SSRS, Columbia-Suicide Severity Rating Scale; aTBS, accelerated theta-burst stimulation.

**Table 1 T1:** Detailed trial schedule.

	Study period							
	Enrollment	Allocation	Post-allocation				Follow-up 1	Follow-up2
Time point	Day-1	Day 0	AFT	Day1	~	Day 10 (Intervention period)	Week2	Week4
Enrollment:								
Eligibility screen	×							
Informed consent	×							
Randomization	×							
Allocation		×						
Interventions:								
Conventional treatment + sequential aTBS								
Conventional treatment + sham sequential aTBS								
Assessments:								
HAMD-17		×				×	×	×
BDI-II		×				×	×	×
C-SSRS		×				×	×	×
P300		×				×		
Case report forms	×							
Adverse events								
TESS								
Blinding			×					
TASS	×							
ATHF	×							

AFT; Immediately post-allocation (after randomization and before the first intervention); HAMD-17, 17-item Hamilton Depression Rating Scale; BDI-II, Beck Depression Inventory-II; C-SSRS, Columbia-Suicide Severity Rating Scale; P300, Electroencephalography; ATHF, Antidepressant Treatment History Form; TASS, Transcranial Magnetic Stimulation Safety Screen; TESS, Treatment Emergent Symptom Scale ×, occurs at that time.

### Patient recruitment

Patient recruitment follows a four-step procedure;

Step 1: Promotion for inpatient recruitment will be conducted through outpatient clinics, among inpatients, and at surrounding community service centers.

Step 2: A clinical research assistant will assess potential participants for eligibility according to the predefined inclusion and exclusion criteria.

Step 3: The study coordinator will schedule an interview with eligible individuals to provide detailed information about the study objectives, procedures, potential risks and benefits.

Step 4: Participants who fully understand the study information and voluntarily agree to participate will provide written informed consent. The written informed consent form is provided in **Supplementary Material S2**.

### Inclusion and exclusion criteria

Inclusion criteria are as follows; meeting the diagnostic criteria for depression as defined by the Diagnostic and Statistical Manual of Mental Disorders, Fifth Edition (DSM-5) (28), or having been taking the same antidepressant for at least two weeks; being Han Chinese residents aged 18 to 60 years; having at least a primary school education; voluntarily agreeing to participate; having a HAMD-17 score ≥17; and having a C-SSRS suicidal ideation score ≥3. Exclusion criteria include meeting the DSM-5 diagnostic criteria for other psychiatric disorders such as schizophrenia or bipolar disorder; being comorbid with poorly controlled severe physical diseases, such as coronary heart disease or thyroid dysfunction; having a history of traumatic brain injury with loss of consciousness or epilepsy; having any severe physical illness requiring long-term medication and/or a history of substance abuse; being pregnant, lactating, or planning pregnant; and having a recent history of fever, acute infection, or contagious diseases. A detailed list of the inclusion and exclusion criteria is presented in **Table 2**.

**Table 2 T2:** Method of ascertainment and justification for inclusion and exclusion criteria.

Inclusion criterion	Method of ascertainment	Justification
Meet the first-episode diagnostic criteria for depression as defined by the Diagnostic and Statistical Manual of Mental Disorders, Fifth Edition (DSM-5), or have been taking the same antidepressant for at least two weeks	Medical records,HAMD-17,BDI-II	Determine the target population of the experiment and medication records
Han Chinese residents aged 18 to 60 years, regardless of gender	Medical records	The population with depression is mainly concentrated in this age group and is suitable for experimental interventions
Educational level of primary school or higher	Directly ask the patient or their family	Be able to cooperate with the intervention and assessment of the experiment
Voluntary participation in the study	Meet with the principal investigator to discuss the study and sign the informed consent form	Required
A score of ≥17 on the 17-item Hamilton Depression Rating Scale (HAMD-17)	The higher the score, the more severe the depressive symptoms are, and a score of ≥17 usually corresponds to “moderate or more severe depression”	Target population of the trial
A score of ≥3 on the Columbia Suicide Severity Rating Scale (C-SSRS) for suicidal ideation	A score of ≥3 on the suicidal ideation dimension indicates the presence of suicidal thoughts with a certain intensity or frequency	Target population of the trial
Exclusion Criteria	Method of ascertainment	Justification
Meet diagnostic criteria for other mental disorders as defined by the DSM-5, such as schizophrenia or bipolar disorder	Medical records, outpatient physician diagnosis	Exclude interference of other diseases on the study
Comorbid with poorly controlled severe physical diseases, such as coronary heart disease or thyroid dysfunction	Medical records, clinical examinations	The study may exacerbate other physical diseases
A history of craniocerebral trauma resulting in loss of consciousness, or a history of epilepsy	Medical records, clinical examinations	Contraindications to transcranial magnetic stimulation (TMS)
Any severe physical illness requiring chronic medication; and/or a history of substance abuse/dependence	Medical records, clinical examinations	The study may exacerbate other physical diseases
Women who are pregnant, lactating, or planning to conceive	Medical records, clinical inquiry	Contraindications to transcranial magnetic stimulation (TMS)
Recent history of fever, acute infection, or contagious diseases	Medical records, clinical examinations	Protect the safety of participants and researchers, and avoid interfering with the accuracy of study results

DSM-5, Diagnostic and Statistical Manual of Mental Disorders, Fifth Edition; TMS, Transcranial Magnetic Stimulation.

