## Introduction

Major depressive disorder (MDD) is a highly prevalent mental health condition in adults, characterized by a lifetime prevalence of 10%-15%, high relapse rates, and particularly severe suicide risk. Suicide remains one of the leading causes of mortality among adults worldwide (1). The central clinical challenge involves suicidal ideation, which affects approximately 60%-80% of adult patients (2). Despite its severity, currently available pharmacological and psychotherapeutic treatments remain limited in their ability to provide rapid stabilization. Antidepressant medications require weeks to exert therapeutic effects, making them unsuitable for acute risk management, while high relapse rates frequently lead to the re-emergence of suicidal ideation even after initial improvement (3, 4). Therefore, there is an urgent need for rapid-acting, safe, and evidence-based interventions specifically targeting suicidal ideation in adults with MDD.

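### The inclusion rule joins DSM-5 depression and antidepressant stability with 'or', so neither is mandatory, and the text and Table 2 disagree on recurrent episodes

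*Protocol article*

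**What the plan says.** The article states the criterion twice in the section on inclusion and exclusion criteria.

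- **Body text.** The first limb is DSM-5 depression, with no mention of episode number. The second limb is "or having been taking the same antidepressant for at least two weeks".
- **Table 2.** The first limb reads "Meet the first-episode diagnostic criteria for depression as defined by the Diagnostic and Statistical Manual of Mental Disorders". The second is again an alternative: "or have been taking the same antidepressant for at least two weeks". The listed method of ascertainment is "Medical records,HAMD-17,BDI-II".

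The other clinical entry conditions are "having a HAMD-17 score ≥17; and having a C-SSRS suicidal ideation score ≥3". The remaining inclusion criteria cover ethnicity and residence, age, education and consent. Among the exclusions is "Meet diagnostic criteria for other mental disorders as defined by the DSM-5, such as schizophrenia or bipolar disorder". No exclusion concerns a recent start or change of an antidepressant.

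The abstract says that 56 adults with MDD will be recruited, and the Objectives set the aim as efficacy in adults with MDD. Routine clinical care continues in both arms (aTBS protocol section). Table 1 schedules an antidepressant treatment history form at enrollment, but no eligibility criterion refers to it.

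**The concern.** Diagnosis and medication stability normally do different jobs. The diagnosis fixes who the results apply to. Stability keeps drug effects that began just before entry out of the outcome window. Joined by 'or', each condition excuses the patient from the other, so the rule secures neither.

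Two groups can enter that the stated aim does not seem to intend. One is patients on an unchanged antidepressant who do not meet DSM-5 depression. The other is patients with DSM-5 depression whose antidepressant was started or changed shortly before baseline. The Introduction itself notes that "Antidepressant medications require weeks to exert therapeutic effects", so a drug begun just before entry could start to act while outcomes are still being collected.

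The first-episode wording adds a direct contradiction. Some patients are eligible or not depending on which of the two statements the screener reads. Patients randomized under inconsistent rules cannot be sorted out afterwards in the analysis without post hoc exclusions.

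**Working it through.** The plan gives no figure on this point, so the check is one of logic. Let D = meets DSM-5 depression, F = first episode, S = same antidepressant for at least two weeks. All patients below are assumed to pass every other criterion. 'No S' covers patients on a recently started or changed drug and patients on no drug.

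- Body text: D or S.
- Table 2: (D and F) or S.

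| Patient | Body text | Table 2 |
|---|---|---|
| D, first episode, S | eligible | eligible |
| D, first episode, no S | eligible | eligible |
| D, recurrent, S | eligible | eligible |
| D, recurrent, no S | **eligible** | **not eligible** |
| no D, S | eligible | eligible |
| no D, no S | not eligible | not eligible |

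Four results follow.

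1. **Diagnosis is not mandatory.** The fifth row is eligible under both statements.
2. **Stability is not mandatory.** The second row is eligible under both, and the fourth under the text.
3. **Text and table conflict in one row only**, the fourth: recurrent depression without two weeks on the same drug.
4. **Treating the diagnosis as implied does not repair the text.** (D or S) and D reduces to D, so the medication limb would then do no work.

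Do the other criteria close the fifth row? The HAMD-17 and C-SSRS thresholds measure severity and suicidal ideation, not diagnosis. Excluding other DSM-5 disorders removes most other psychiatric reasons for taking an antidepressant. It does not turn MDD into a requirement: a patient who meets criteria neither for depression nor for another disorder, but scores above both thresholds on a stable drug, still passes.

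**When recent drug changes would matter.** T1 follows 10 weekday sessions, so a drug begun the day before baseline has been taken for only about two weeks by then. On the Introduction's own statement about onset, its effect should show mainly at T2 and T3. The primary comparison is made after the intervention and is less exposed.

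**Size.** The documents give neither response rates by arm nor a share of newly medicated patients. As an illustration only, assume response of 20% on sham and 50% on active with 25 completers per arm. Exact power of the chi-square test at two-sided 0.05 is 0.638. If recent drug changes raise both arms by 10 points (30% against 60%), it is 0.622, a loss of about 2 points.

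**The case against.** **The intended meaning may be sound.** The authors may have meant depressed patients who are either in a first episode or already treated and stable. The abstract speaks of adults with MDD, Figure 1 of depressed patients, and two practicing physicians carry out screening. That makes substantial enrollment of patients without MDD unlikely, and the documents do not show that it would occur. But no sentence states this meaning, and the body text drops the first-episode wording on which it depends. The recruitment section has a research assistant apply the criteria as predefined.

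**A reader might infer that recent drug changes confound the comparison.** The documents do not support that. Allocation is randomized and concealed in sealed envelopes, so any imbalance in newly medicated patients is chance, which the test's error rate already covers.

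**A reader might also infer a large loss of power.** If only the sham rate rose, from 20% to 30% against 50%, power would fall to 0.334. Chance imbalance cannot plausibly do that. Ten points of 28 patients is 2.8 extra responders. From an excess of 3 to 4 newly medicated sham patients, 2.8/4 = 70% to 2.8/3 = 93% would have to become responders because of the drug. With an assumed 30-point drug effect, 3.5 extra patients give 3.5 × 0.30 / 28 = 3.75 points, or about 24% against 50% and power of about 0.51. Even that needs the imbalance to fall on the sham side. The probability of a sham excess of 3 or more is about 6% if 4 of 56 patients are newly medicated, 10% if 6 and 20% if 20. All these shares are assumptions.

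**A reader might take the contradiction as a first-episode trial against an any-episode trial.** That goes too far. Table 2's second limb still admits recurrent patients on a stable drug.

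**A reader might say that the diagnosis rests on severity scales alone.** Medical records stand first in the listed method, and the row also covers medication history. This is minor.

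What stands of the objection is that the consequences are limited. It does not remove the defect in the rule.

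**Conclusion.** The point holds as a defect in the eligibility rule. Under both statements of the criterion an MDD diagnosis is not required and a stable antidepressant is not required. The two statements contradict each other for recurrent patients without two weeks on the same drug. The rule therefore does not secure the population to which the trial attributes its results.

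The statistical consequence is modest: a less clearly defined population, and added outcome noise from recent antidepressant changes, mainly at T2 and T3. There is no systematic bias. No power figure should be attached to the point, since every one depends on response rates and medication shares that the documents do not give. In the symmetric illustration the loss is about 2 points.

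The conclusion about eligibility rests only on the wording of the criteria and needs no numerical assumption. It is worth correcting firmly because it decides who may be enrolled.

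**What to change.** 1. Make the DSM-5 MDD diagnosis a separate inclusion criterion that every participant must meet.
2. State the protocol's existing two-week antidepressant condition as a separate criterion, and say to whom it applies (for example, whether it binds only patients taking an antidepressant, and how unmedicated patients are handled). That choice belongs to the sponsor.
3. Use identical wording in the body text and Table 2 on whether recurrent episodes are eligible. Which version is meant is also for the sponsor to decide.

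The cost is a short wording amendment, carried through to the screening form, and possibly a few candidates who would have qualified under the present wording. No change to sample size, visits or analysis is needed. If patients have already been enrolled, record which limb each one met, so that the report can describe the population accurately.
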